### Demographic and baseline disease characteristics

Baseline descriptive statistics of the study cohort will be stratified by arm, with the sample sizes reported for each arm. Mean (standard deviation) and median (interquartile range) will be reported for numerical outcomes as appropriate. Frequency and proportion will be reported for categorical outcomes. These statistics will be reported for both the intention-to-treat population and the per protocol population.

### Efficacy analysis

Efficacy analysis will be performed on all primary and secondary efficacy endpoints. Point estimates, interval estimates (95% confidence interval) and p-values will be reported.

***Primary efficacy endpoint*.** The primary outcome is Frailty status measured by SHARE-FI at three months of follow-up.

Changes in proportions in non-frail, pre-frail and frail categories will be analysed in both study arms and reported as an odds ratio with associated 95% confidence intervals and tested for significance using a standard chi-square test of proportions.

We hypothesise that participants on resistance exercise regime and with guidance on dietary protein will have a higher SHARE-FI score than patients without this intervention.

This outcome will be analysed as a difference in means between treatment arms using a linear mixed effects model, with arm allocation, SHARE-FI at baseline and age included as fixed effects and GP practice included as a random effect.

***Secondary efficacy endpoints*.** Clinical frailty status measured by CFS at three months will be analysed using a proportional odds mixed model with arm allocation and age as fixed effects and GP practice as random effect. Muscle mass measured by bioelectrical impedance at three months will be analysed using a logistic mixed model with arm allocation as fixed effect and GP practice as random effect.

Ease of the intervention measured on a five-point scale and difference to general health as a result of the exercises measured on a five-point scale will be analysed using a proportional odds model with arm allocation as covariate.

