### Feasibility study

Feasibility of the exercise component of the intervention was assessed in a study in 2019 and 2020
^12^. The findings have been key to refining the intervention for this RCT. We offered an exercise intervention to reverse frailty and build resilience in primary care consultations. We set out to assess uptake of the exercise regime; ratings of its ease and subjective health after participation; how a follow-up telephone-call might affect compliance and overall feasibility. We applied the Bowen feasibility model
^13^ which has been successfully used in assessing public health and preventive medicine interventions. This feasibility model tests eight areas of focus: acceptability; demand; implementation; practicality; adaptation; integration; expansion; and limited-efficacy testing. Selected results include:

A total of 94 of 107 eligible people (88%) participated (average age 77, 59 females (63%)). 95% of females and 78% of males enrolled. Only 15% had previously considered resistance exercises.

Participants found the exercises both easy to follow and generally easy to do. Overall, 32% described exercises as ‘very easy’, 55% ‘somewhat easy’, 7% ‘neither easy nor hard’, 6% ‘somewhat hard and 0% ‘very hard’.

At one month, 66% of participants called were exercising regularly (76% of females, 50% of males). At two months, compliance among those who had not been called at one month was: 65% (67% of females, 62% of males). However, compliance among those previously called was higher: 78% (88% of females, 63% of males). 64% of those who were not doing exercises at one month had taken them up following the single phone call (67% of females, 63% of males).

Many described how the home-based exercises helped with staying active and reducing anxiety while housebound during the Covid-19 pandemic

The majority of participants self-reported their general health had improved as a result of doing the exercises and none reported feeling worse. 14% felt ‘much better’, 52% ‘slightly better’, 34% ‘about the same’, 0% ‘slightly worse’, and 0% ‘much worse’

Each of the eight areas of focus of the Bowen feasibility model have been addressed and satisfy overall feasibility. Publication of this feasibility study is pending.

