### Study methods, assessments and procedures

GP site investigators will undergo three team-based training sessions prior to enrolment, monthly meetings after enrolment and additional ad-hoc meetings when required, led by the principal investigator, in order to standardise the approach and align to this study protocol, including patient communication, intervention delivery and data gathering and management.

Adults attending a GP surgery, meeting the eligibility criteria, will be offered general information about the study by the attending GP. If interested and willing to consent, they will be offered an information leaflet for the trial, and invited to participate. Participants will be randomly assigned to ‘intervention’ or ‘usual care’ parallel arms.

Participants randomly assigned to the usual care group will receive normal primary care, including physical rehabilitation if needed.

Intervention participants will be provided a leaflet with strength exercises and a discussion on how strength exercises have been shown to delay and reverse frailty and build resilience. The information leaflet will have a photographic overview of a home-based exercise regime. They will also be provided with information on post exercise protein consumption as part of a normal balanced diet.

Baseline measurements for all recruited patients will be: age, sex, education, living arrangement (alone, with others), smoking status, alcohol intake, blood pressure, heart rate, BMI (weight and height), comorbidities, malnutrition universal screening tool (MUST), CFS, SHARE-FI (which includes handgrip strength) and bioelectrical impedance for muscle mass, body fat, bone weight, base metabolic rate and ‘biological age’. Bioelectrical impedance will be measured using a Tanita RD 545 Segmental Body Composition Analyser, with dual frequency technology and medical grade accuracy.

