### Safety analysis

Incidence of in-patient hospitalisation during follow-up and incidence of LTC during follow up will be analysed using a logistic regression model with arm allocation and age as covariates.

All non-serious and serious AEs will be reported in tables in aggregate form by frequency and subjects affected by trial arm.

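### Sex is collected at baseline but appears in none of the stated outcome models; the choice is permissible but gives away precision, mainly for muscle mass

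*Protocol article*

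**What the plan says.** Under Study methods, assessments and procedures, the baseline list opens "Baseline measurements for all recruited patients will be: age, sex, education, living arrangement (alone, with others", so sex is available for everyone. The same list includes "SHARE-FI (which includes handgrip strength" and bioelectrical impedance for muscle mass and other body-composition measures. The Randomisation section describes simple 1:1 allocation, with no stratification.

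The covariates of the models are stated in Efficacy analysis and Safety analysis:

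- SHARE-FI at three months: a linear mixed model "with arm allocation, SHARE-FI at baseline and age included as fixed effects and GP practice included as a random effect".
- CFS: a "proportional odds mixed model with arm allocation and age as fixed effects and GP practice as random effect".
- Muscle mass: a "logistic mixed model with arm allocation as fixed effect and GP practice as random effect".
- Ease of the intervention and change in general health: proportional odds models with arm alone.
- Hospitalisation and long-term care admission: a "logistic regression model with arm allocation and age as covariates".

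Sex is in none of them. The article names no separate model for body fat, bone weight, metabolic rate or biological age.

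**The concern.** Adjusting for a baseline variable that predicts the outcome reduces residual variance in a linear model and removes the effect of any chance imbalance in that variable. Sex is an obvious candidate where the outcome is a body-composition measure or contains grip strength. It costs nothing to collect here, and simple randomisation does nothing to balance it. At stake are wider confidence intervals than the data need give, and a muscle-mass comparison that is more sensitive to the sex mix each arm happens to receive. Because the covariate lists are written out, this concerns a stated analysis and not a detail left to the SAP.

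**Working it through.** **Inputs.** From the protocol: 176 evaluable and 210 enrolled participants, 1:1 allocation, response rates of 15% and 3%, 5% type I error, 80% power. From the feasibility study: 63% women, assumed here to hold in the trial. The article gives no association between sex and any outcome, so every R² below is an assumption shown as a range.

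**1. The plan's own sample size.** The two-sided pooled formula is n per arm = [1.960 × √(2 × 0.09 × 0.91) + 0.842 × √(0.15 × 0.85 + 0.03 × 0.97)]² / 0.12² = (0.793 + 0.333)² / 0.0144 ≈ 88.1. That is 89 per arm (178) rounded up, or 88 (176) rounded to nearest; power at 88 per arm is 79.96%. Dropout: 176 / 0.85 = 207.1, so 208 in equal arms, consistent with 210. The calculation compares two unadjusted proportions and does not depend on any covariate.

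**2. Chance imbalance in sex.** SD of the between-arm difference in the proportion of women = √(4 × 0.63 × 0.37 / N).

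- N = 210: 6.7 points; a difference above 10 points arises in about 13% of randomisations.
- N = 176: 7.3 points; about 17%.

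**3. Muscle mass, no other fixed covariate, linear scale.** SE ratio after adding sex = √(1 − R²). The sex difference in outcome SD units is √R² / √(0.63 × 0.37) = √R² / 0.483. A 10-point imbalance shifts the unadjusted arm difference by 0.10 times that. The unadjusted SE at N = 210 is √(4/210) = 0.138 SD.

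| Assumed R² of sex | Cut in SE | Shift from a 10-point imbalance |
|---|---|---|
| 20% | 11% | 0.09 SD |
| 40% | 23% | 0.13 SD |
| 60% | 37% | 0.16 SD |

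**4. SHARE-FI, baseline and age already in the model.** Same SE ratio, with R² now the partial R² of sex. Equivalent extra participants = 210 / (1 − R²) − 210. Power is set against an illustrative 80% at N = 176.

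| Assumed partial R² | Cut in SE | Equivalent extra participants | Power |
|---|---|---|---|
| 1% | 0.5% | 2.1 | 80.4% |
| 2% | 1.0% | 4.3 | 80.8% |
| 5% | 2.5% | 11.1 | 82.0% |

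**5. Do the feasibility compliance gaps make sex prognostic?** Suppose sex acts only through compliance in the intervention arm, and complying shifts the outcome by E SD. The sex coefficient pooled over arms is (gap × E) / 2, and R² = coefficient² × 0.63 × 0.37. With the widest gap (76% v 50%, 26 points) and a generous E of 0.8, the coefficient is 0.104 and R² is 0.0025. With E of 0.3 it is 0.0004. This route yields almost nothing.

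**The case against.** The strongest objection is that nothing here is wrong. The primary model already contains the baseline score, age and practice. Sex is not a stratification factor that the analysis then ignores, and no statement in the article commits to adjusting for it. That stands: this is an improvement, not a correction. It also stands that the R² values have no source in the article, and that the article nowhere gives a sex difference in grip strength or muscle mass. For muscle mass such a difference is hard to doubt; its size is assumed.

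A further fair point is that the muscle-mass and CFS models lack the outcome's own baseline value, which is the larger omission. Adjusting for baseline muscle mass would capture much of what sex offers, so the two gains overlap and must not be added.

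A reader might go further in four ways that the documents do not support:

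- *Sex is the best predictor of uptake, and uptake makes it prognostic.* The feasibility study reports "At one month, 66% of participants called were exercising regularly (76% of females, 50% of males" and, at two months, "compliance among those previously called was higher: 78% (88% of females, 63% of males". It also reports 67% v 62% among those not called, and 67% v 63% for take-up after a call. Sex is the only participant characteristic broken down, so no ranking is possible. Enrolment precedes randomisation, and in the trial compliance with the regime belongs to the intervention arm. At most this hints at effect modification, which a main-effect term does not address.
- *Chance imbalance biases the result.* Over randomisations it does not, and the standard error allows for it.
- *Missing-data assumptions are weakened.* The article gives no missingness by sex, and its imputation statement lists no variables, so it does not exclude sex.
- *The same gain applies to CFS.* The √(1 − R²) rule is for linear models. In proportional odds or logistic models an added covariate changes the conditional odds ratio and need not reduce its standard error.

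**Conclusion.** The point holds as a minor, optional improvement. Sex is collected, left out of every stated model and not balanced by design; omitting it is permissible and does not invalidate any analysis. The loss is material only for muscle mass and probably the other body-composition measures. There, on a continuous scale, the standard error could fall by roughly a tenth to over a third if sex explains 20% to 60% of the variance, and a 10-point imbalance could move an unadjusted estimate by about as much as its standard error (0.09 to 0.16 SD against 0.14 SD). For SHARE-FI the gain is probably slight. The figures assume 63% women, ignore practice effects, and rest on assumed R² values; the muscle-mass figures do not carry over to the logistic model now stated.

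**What to change.** Before unblinded data are seen, prespecify sex as a fixed effect, together with the outcome's own baseline value, in the models for muscle mass and the other body-composition measures, and analyse these on the continuous scale with a linear mixed model. Optionally add sex to the SHARE-FI linear mixed model. Where sex is left out, one sentence giving the reason would suffice.

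The cost is one degree of freedom per model for sex and a short amendment to the analysis text. No new data are needed, and the sample size is unaffected.

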## Study objective

### Primary objective

To measure changes in health outcomes, including physical frailty status (SHARE-FI), clinical frailty status (CFS), muscle-mass, as a result of an optimised exercise and dietary intervention versus usual care among community-dwelling adults aged 65 and over whose baseline clinical frailty (CFS) is not worse than mild.

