***Inclusion criteria***

 Aged 65 or older at baseline Rockwood clinical frailty scale score 4 or 5 (vulnerable or mildly frail) Able and willing to provide informed consent and to comply with the requirements of this study protocol

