### Method of assigning participants to treatment groups

***Randomisation*.** Randomisation of participants will be done on a 1:1 allocation to intervention or usual care by a simple randomisation procedure, guided by the Clinical Research Centre (CRC) team. We will use a randomisation software product provided by the American National Cancer Institute.

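### The three-month CFS model leaves out baseline CFS: still valid, but it gives up precision and leaves chance imbalance uncorrected

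*Protocol article*

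**What the plan says.** Under Efficacy analysis (secondary efficacy endpoints), CFS at three months is to be "analysed using a proportional odds mixed model with arm allocation and age as fixed effects", with a random effect for GP practice. The covariates are listed in full, and baseline CFS is not among them.

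Four other places bear on this:

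- **Primary SHARE-FI model, same section.** It does carry its own baseline: "SHARE-FI at baseline and age included as fixed effects".
- **Study methods, assessments and procedures.** The list that opens "Baseline measurements for all recruited patients will be" includes "malnutrition universal screening tool (MUST), CFS, SHARE-FI (which includes handgrip strength".
- **Inclusion criteria.** Entry requires "Rockwood clinical frailty scale score 4 or 5 (vulnerable or mildly frail", so CFS must be known before anyone is enrolled.
- **Method of assigning participants to treatment groups.** Allocation is 1:1 "by a simple randomisation procedure". No stratification by CFS is mentioned.

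The primary objective is "To measure changes in health outcomes, including physical frailty status (SHARE-FI), clinical frailty status (CFS), muscle-mass" under the intervention against usual care.

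**The concern.** The objective speaks of change, but the CFS model compares three-month values without using where each participant started. The article adjusts for baseline on one frailty scale and not on the other, and gives no reason. Baseline CFS should be complete, because it decides eligibility.

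Two things are at stake for this secondary outcome. The first is power: if entry CFS predicts CFS three months later, leaving it out discards usable information. The second is how a particular result will be read. If one arm happens to enrol more people at CFS 5, that arm will tend to look worse at three months even with no treatment effect. Neither the design nor the model corrects for this, apart from whatever age captures.

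**Working it through.** **The plan's own figure.** The only sample size is for the primary outcome (15% v 3%, 5% type I error, 80% power, 1:1). With two-sided alpha and pooled variance, n per arm = [1.96·√(2·0.09·0.91) + 0.8416·√(0.15·0.85 + 0.03·0.97)]² / 0.12² = (0.793 + 0.333)² / 0.0144 ≈ 88.1. Rounded up, this is 89 per arm or 178 in total, against 176 stated, so it is reproduced. After 15% dropout, 210 × 0.85 = 178.5. No figure is given for CFS; the checks below use 178 patients.

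**Inputs the documents do not give (assumed).** The share at CFS 5 (30% or 50%), the conditional treatment log-odds (0.8 or 0.9), and the log-odds coefficient for baseline CFS 5 v 4 (0 to 4).

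**Step 1: how far simple randomisation can drift.** The SD of the arm difference in the CFS 5 share is √(4p(1−p)/N).

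| N | p | SD (points) | P(difference ≥ 10 points, either way) |
|---|---|---|---|
| 178 | 0.3 | 6.9 | 14.5% |
| 178 | 0.5 | 7.5 | 18.2% |
| 210 | 0.3 | 6.3 | 11.4% |
| 210 | 0.5 | 6.9 | 14.7% |

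At N = 210 and p = 0.5, the 95% range is ±1.96 × 6.9 = ±13.5 points.

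**Step 2: power and type I error.** Proportional odds simulation: 178 patients, 1,500 trials per row, treatment log-odds 0.9, four CFS levels at follow-up. Both models contain arm and age. The practice effect was left out for simplicity, and age was generated independently of baseline CFS.

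| Share at CFS 5 | Baseline log-odds | Power without | Power with | Loss (points) |
|---|---|---|---|---|
| 30% | 0 | 86.5% | 86.5% | 0 |
| 50% | 0 | 87.4% | 87.3% | 0 |
| 30% | 1.5 | 79.7% | 84.5% | 5 |
| 50% | 1.5 | 82.3% | 87.2% | 5 |
| 30% | 3.0 | 68.9% | 85.8% | 17 |
| 50% | 3.0 | 61.3% | 82.6% | 21 |
| 30% | 4.0 | 51.3% | 79.2% | 28 |
| 50% | 4.0 | 45.9% | 78.5% | 33 |

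The Monte Carlo standard error is about 1 point (√(0.8·0.2/1500) = 1.0). Only comparisons within a row are fair, because the assumed cut points change with the baseline coefficient. With no treatment effect, the rejection rate was 4.3% to 5.9% without baseline CFS and 4.2% to 6.3% with it.

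A separate simulation at treatment log-odds 0.8, also with 178 patients, gave 72% v 72% at baseline log-odds 0, 83% v 83% at 1, 65% v 79% at 2 and 60% v 77% at 3. Adjustment cost no power beyond simulation error in either.

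**Step 3: what an imbalanced trial would show.** Take the trials with no true effect and over 10 points more CFS 5 in the intervention arm. Without baseline CFS the estimated log-odds moves against the intervention by about 0.20 at coefficient 1.5, 0.32 to 0.35 at 3.0 and 0.36 to 0.38 at 4.0. With baseline CFS the shift is at most 0.05.

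A hand check agrees. For a normal difference with SD 0.075, the mean beyond 0.10 is 0.075 × 0.164/0.0912 ≈ 0.13, and 1.5 × 0.13 ≈ 0.20.

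**The case against.** The strongest reply is that this is a choice about efficiency, not an error. Comparing three-month CFS between randomised arms needs no baseline term to be valid. The confidence interval already allows for chance imbalance, and baseline characteristics will be reported by arm, so a large imbalance would be seen. CFS is one of several secondary outcomes and no power is claimed for it. All of this stands.

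Two stronger readings are tempting, and the documents do not support them.

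- **That the CFS comparison is biased or has an inflated error rate.** Over all randomisations it does not: type I error stays at about 5%. The shift in step 3 is conditional on an imbalance having occurred.
- **That the unadjusted odds ratio is wrong because it is smaller.** In the simulation the mean log-odds was 0.85 at coefficient 1.5, 0.64 to 0.70 at 3.0 and 0.52 to 0.57 at 4.0 without baseline CFS, against 0.90 to 0.93 with it. These are averages over trials in which imbalance cancels out. The gap is largely non-collapsibility: the two models estimate different odds ratios. Power is the fair comparison.

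It is also fair to object that large losses need strong associations. Log-odds of 2 and 3 are odds ratios of about 7 and 20, and entry is restricted to two adjacent categories. The documents do not show how well CFS 4 v 5 predicts CFS three months later. Where age tracks CFS, the age term would recover some of the loss.

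What the reply does not do is give a reason for leaving the term out, when the SHARE-FI model in the same section adjusts for its own baseline.

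**Conclusion.** The point holds as a recommendation for precision and consistency. The stated CFS analysis is valid, but it gives up information that the trial collects on everyone and leaves a chance imbalance uncorrected, except through age.

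Under the assumed values, the power loss is nil if baseline CFS has no association with three-month CFS, about 0 to 5 points at baseline log-odds of 1 to 1.5, and about 15 to 30 points at 2 to 4. Which part of that range applies cannot be read from the documents. No association at all is implausible for the same scale three months apart, but the upper end should not be taken as the expected loss. An imbalance of 10 points or more in the CFS 5 share has a chance of roughly 11% to 18%.

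The primary analysis and the sample size are not affected.

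**What to change.** Add baseline CFS as a categorical fixed effect to the proportional odds mixed model for three-month CFS. Keep arm, age and the GP practice random effect. Specify this before any unblinded analysis; the same adjustment added after an imbalance has been seen would look post hoc.

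Under the Inclusion criteria the categories are 4 and 5. The abstract, the Rationale and the primary objective describe entry more loosely (CFS of 5 or less, or no worse than mild). Those statements should be reconciled so that the coding covers everyone enrolled.

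No new data, visits or patients are needed, and the model gains one parameter if there are two categories. The article requires deviations from the statistical plan to be reported in writing to the research ethics committee and approval sought, so the change should go by that route or as a protocol amendment. If the SAP, which was not available for this review, already includes the term, the two documents only need to be aligned.

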***Secondary outcomes***

 Clinical frailty status measured by CFS at three months after the start of intervention. Muscle mass measured by bioelectrical impedance at three months after the start of intervention.Body fat, bone weight, base metabolic rate, biological age by bioelectrical impedance at three months after the start of intervention. Incidence of in-patient hospitalisation during follow-up. Incidence of long-term care admission (LTC) during follow-up. Ease of the intervention measured on a five-point scale: ‘very easy’, ‘somewhat easy’, ‘neither easy nor hard’, ‘somewhat hard’, or ‘very hard’ three months after the start of intervention. Difference to general health as a result of the exercises measured on a five-point scale: ‘much better’, ‘slightly better’, ‘about the same’, ‘slightly worse’ or ‘much worse’ three months after the start of intervention.

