### Determination of sample size subjects

We have calculated a sample size of 176 with the following parameters: Two independent study groups (i.e., control and intervention); outcome measure of frailty status (i.e., change from frail or pre-frail to non-frail as measured by SHARE-FI); improvement of frailty status in the intervention group to non-frail of 15%, allowing for a 3% improvement in the control group due to bias; enrolment ratio of 1; probability of type I error of 5% (0.05); power 80%. Enrolment of 210 participants assumes a 15% drop out rate.

Sample sizes in comparable trials include Binder, J Am Geriat Soc 2002 (sample size 115)
^20^, Liu, Clin Rehab 2017 (sample size 79)
^21^ and Serra-Prat, Age Aging 2017 (sample size 172)
^2^. The average study size of the 31 studies included in our meta-analysis of frailty interventions
^7^ was exactly 100.

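### The protocol names a logistic mixed model for three-month muscle mass, a continuous measurement with no binary definition, so the model cannot be fitted as written

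*Protocol article*

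**What the plan says.** The protocol article treats muscle mass as follows.

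- **Primary objective:** "To measure changes in health outcomes, including physical frailty status (SHARE-FI), clinical frailty status (CFS), muscle-mass", comparing the intervention with usual care.
- **Secondary outcomes:** "Muscle mass measured by bioelectrical impedance at three months after the start of intervention". No threshold, category or event is attached to it.
- **Study methods, assessments and procedures:** the baseline measurements for all recruited patients include "bioelectrical impedance for muscle mass, body fat, bone weight, base metabolic rate".
- **Efficacy analysis, secondary endpoints:** "Muscle mass measured by bioelectrical impedance at three months will be analysed using a logistic mixed model with arm allocation as fixed effect", with GP practice as a random effect. Arm is the only fixed effect.

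For comparison, the SHARE-FI score in the same section gets a linear model: "This outcome will be analysed as a difference in means between treatment arms using a linear mixed effects model". That model adjusts for each participant's own starting score and for age, and carries a practice-level random effect. CFS, an ordinal scale, gets a proportional odds mixed model. Under Safety analysis, hospitalisation and long-term care admission are the outcomes for which the plan says each "will be analysed using a logistic regression model with arm allocation and age as covariates".

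**The concern.** Logistic regression models the probability of an event. Muscle mass from a body composition analyser is a quantity, and the article never turns it into an event. A statistician who follows the sentence literally has no response variable to enter.

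There are two ways out. One is to depart from the stated model, which the section on deviations from the statistical plan says must be reported to the ethics committee with approval sought. The other is to choose a cut-off that the protocol does not contain. That choice would not be pre-specified, and dichotomising discards information.

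A second, lesser matter is the missing baseline covariate. Muscle mass is measured in everyone at entry and the objective speaks of change, but the model ignores the starting value.

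At stake is the estimate for an outcome that the primary objective names.

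**Working it through.** **1. Does each named model fit its outcome?**

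| Outcome | Type as defined | Model named | Fits? |
|---|---|---|---|
| SHARE-FI score | continuous score | linear mixed, own baseline included | yes |
| CFS | ordinal | proportional odds mixed | yes |
| Hospitalisation, long-term care admission | binary incidence | logistic | yes |
| Muscle mass | continuous measurement | logistic mixed | no |

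The only text that could supply a category is in Rationale for the study, where sarcopenia is said to have been operationalised by consensus. It states no threshold, and no sarcopenia category appears among the outcomes.

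**2. The plan's own figure.** The only computed figure is the primary-outcome sample size: "We have calculated a sample size of 176 with the following parameters". The inputs are 15% against 3%, 1:1 allocation, 5% type I error (two-sided assumed) and 80% power. The pooled two-proportion formula without continuity correction is

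n per arm = [1.960·√(2·0.09·0.91) + 0.842·√(0.03·0.97 + 0.15·0.85)]² / 0.12² ≈ 88.1, which rounds up to 89, or 178 in total.

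Power at 88 per arm is 79.96%, so 176 reproduces to within two participants. With 15% dropout, 176/0.85 = 207.1, or 208 as an even number, close to the stated 210. None of this depends on muscle mass. I carry 88 per arm forward as the analysable number.

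**3. Cost of leaving baseline out, under a linear model.** The documents give no SD, target difference or correlation for muscle mass, so results are in SD units over assumed correlations r between baseline and three months. Practice effects are ignored.

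Detectable difference = (1.960 + 0.842)·√(1 − r²)·√(2/88) = 0.422·√(1 − r²)

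| r (assumed) | √(1 − r²) | Detectable difference (SD) |
|---|---|---|
| baseline not used | 1 | 0.42 |
| 0.5 | 0.866 | 0.37 |
| 0.7 | 0.714 | 0.30 |
| 0.8 | 0.600 | 0.25 |
| 0.9 | 0.436 | 0.18 |

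**4. Cost of making the logistic model fittable with a cut-off.** Take a true difference of 0.422 SD, at which the unadjusted linear comparison has 80% power, and assume normal data. The cut-off turns the difference into two proportions, which are compared with 88 per arm.

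- **Median split:** Φ(0.211) ≈ 0.58 against 0.42; power about 60%.
- **Cut at the 30th centile of the reference arm:** power about 52%.
- **20th centile:** about 43%.
- **10th centile:** about 30%.

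Steps 3 and 4 concern different faults and should not be combined.

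**The case against.** Much can be said on the other side.

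- *Logistic* may be a slip for *linear*, or the authors may have meant a low-muscle-mass category whose cut-off sits in an analysis plan not shown here. Either is possible; the text settles neither. This is still more than an omission that an article may leave to another document, because the protocol names a specific model that does not match its own outcome definition.
- A reader might infer that omitting baseline also makes the effect biased or inestimable. It does not. Randomisation protects the comparison, and only precision is lost. Nor is muscle mass a lone exception: the CFS model omits its own baseline too.
- A reader might infer that muscle mass is the trial's only device-measured outcome and therefore carries special weight. The Secondary outcomes section lists body fat, bone weight and other bioimpedance readings, and SHARE-FI includes handgrip strength.
- A reader might claim a several-fold gain in effective sample size from baseline adjustment. That needs high assumed correlations. At r = 0.5 the detectable difference moves only from 0.42 to 0.37 SD.
- That a cut-off would be picked after looking at the data is speculation. What can be said is that none is stated.

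The mismatch between model and outcome survives all of these. The objections limit how much weight it can bear.

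**Conclusion.** The point holds in a limited form. The mismatch follows from the text and needs no assumption: as written, the analysis yields no estimate of a muscle-mass difference. If a cut-off were used to rescue it, power would fall from 80% to roughly 30–60% in the illustration, depending on where the cut falls and assuming normal data.

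The missing baseline is a separate question of efficiency, worth between 0.05 SD (0.42 to 0.37) and 0.24 SD (0.42 to 0.18) in detectable difference for correlations of 0.5 to 0.9. Those correlations are assumptions.

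A reader might take muscle mass's place in the primary objective to mean that the trial's main conclusion is in doubt. The documents do not support that. SHARE-FI is the primary outcome, and neither its analysis nor the sample size uses muscle mass. This is a wording error on a secondary endpoint that should be corrected before analysis.

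**What to change.** Replace the muscle-mass sentence under Efficacy analysis with wording such as: *Three-month muscle mass will be analysed with a linear mixed model with arm allocation and baseline muscle mass as fixed effects and GP practice as a random effect; the adjusted mean difference between arms will be reported with its 95% confidence interval.*

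Age and sex may be added as fixed effects but are optional. Age is already in the SHARE-FI and CFS models; sex is in none of the models in the article.

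If a binary low-muscle-mass outcome was intended, keep the logistic mixed model but add the definition and its cut-off to the outcome list before any outcome data are seen.

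The cost is one sentence, submitted through the ethics committee route that the protocol already sets out for amendments. No new data are needed, since baseline muscle mass is already collected, and the sample size does not change.
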